## 2. Materials and Methods

### 2.1. Setting and Design

This study is a multicenter, cross-sectional, clinical observational study using a case–control design. Data will be collected in outpatient, inpatient, and day-clinic settings of Child and Adolescent Mental Health clinics. The CAPE interview is conducted with the primary caregiver and evaluated by a clinician (LPE, yes/no). Standardized questionnaires are rated by the primary caregiver (external report) and the child (self-report).

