### 2.2. Sampling Method, Recruitment, and Procedure

Participants are recruited from two independent clinical sites to improve the generalizability of results and to minimize potential site-specific biases. Parents of children/adolescents undergoing outpatient, inpatient, or day-clinic treatment, or who are on a waiting list for aggressive behavior treatment and diagnosed with DBD, will be contacted by telephone (Figure 1). If interested, study information and consent forms will be sent by post, and an appointment will be scheduled with the primary caregiver and child for data collection. The personal appointment at the Child and Adolescent Mental Health Department will last approximately 1.5 to 2 h. Participants and their primary caregivers are informed about the study, the voluntary nature of participation, data storage, and the procedural aspects involved. After the consent forms are signed, a trained clinician (e.g., a licensed child and adolescent psychotherapist or a trained physician) conducts the CAPE interview with the primary caregiver.

Additionally, the primary caregiver and child complete standardized questionnaires using the electronic data collection software SoSciSurvey^©^ (Version 3.5.07; Leiner, 2024) on a tablet. Due to the study’s format, completion of the study is contingent upon entering all data, thereby ensuring that no entries are missing. As part of the study, the questionnaires are read out to all children. They also have the opportunity to ask questions to make sure they understand. To reduce shared method variance and potential circularity in the validation analyses, SPJ are derived independently from the questionnaires. All families are offered a diagnostic and clarification phase for DBD regardless of their child’s LPE status on the CAPE. Each family is informed that they can share the CAPE results with their psychotherapist or physician.

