### 2.4. Sample Size Calculation

In line with earlier findings (Colins et al., 2020; Goetz et al., 2024; Hawes et al., 2020; Molinuevo et al., 2020; Neo et al., 2023), we expect medium-to-large effect sizes for research question one when examining and comparing children with and without LPE across relevant convergent/divergent constructs (DBD and social competence, reactive/proactive aggressive behavior, emotion recognition, and empathy). Based on two groups (LPE, yes/no) in an analysis of covariance (ANCOVA), we can estimate, using G*Power 3.1 (effect size = 0.50, α = 0.05, 1−β = 0.95), that a total sample size of 55 would yield statistically significant results. We expect small-to-medium effect sizes when examining LPE correlations with relevant convergent/divergent constructs. Based on calculations (effect size = 0.40, α = 0.05, 1−β = 0.95), we can assume that a sample size of 63 patients would yield statistically significant results. In this context, moderate effects are also assumed when calculating incremental validity via hierarchical regression (effect size = 0.15, α = 0.05, 1−β = 0.95; number of tested predictors: 2; total number of predictors: 7), yielding an *N* of 83.

For research question two, children and adolescents with elevated CU traits will be separated into two groups based on whether they have primary or secondary CU traits, depending on at least two interpersonal potential traumatic events and high anxiety scores. Groups will be compared in levels of anxiety, depression scores, emotion recognition, empathy, DBD, and social competence, and reactive/proactive aggressive behavior (Bennett & Kerig, 2014; Craig et al., 2021; Craig & Moretti, 2019; Dadds et al., 2018; Kahn et al., 2013; Kimonis et al., 2012, 2013; Mozley et al., 2018; Robertson et al., 2023; Vasileva et al., 2019). According to Kimonis and colleagues (Kimonis et al., 2012, 2013), medium-to-high effect sizes are expected (Cohen’s *d* = 0.41–0.96). Kahn and colleagues (Kahn et al., 2012, 2013) reported small-to-medium effect sizes. Hence, we require an *N* of 84 (ANCOVA; G*Power: effect size = 0.40, α = 0.05, 1−β = 0.95) to estimate the required sample size. To adequately address the research question, an *N* of 84 participants is required. Given a 20% attrition rate, this would correspond to 101.

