### 2.5. Outcomes

**Clinical Assessment of Prosocial Emotions (CAPE)**

The *Clinical Assessment of Prosocial Emotions* 1.1 (CAPE 1.1 (Frick, 2013)) is a semi-structured interview developed for clinicians to assess CU traits according to DSM-5 criteria in children and adolescents diagnosed with DBD: (a) lack of remorse or guilt, (b) callousness-lack of empathy, (c) unconcerned about performance, and (d) shallow or deficient affect. The interview can be given to the child, parents, teachers, or other caregivers for an SPJ for LPE. In the study at hand, the primary caregiver will be interviewed by a trained and licensed children and adolescent psychotherapist or a trained physician from the Child and Adolescent Mental Health team. We ensure that all CAPE assessments are conducted with legal authorization to perform clinical assessments and with at least three years of experience conducting and evaluating clinical interviews with children and adolescents. These professionals were trained in psychopathology, child development, clinical interviewing, ethical standards, the research literature on CU traits, and the administration and scoring procedures of the CAPE. They are also continuously supervised by the study directors and can ask questions. The interview was translated into German using the TRAPD method (translate, review, adjudication, pretest, documentation) (Curtarelli & van Houten, 2018). During the interview, primary caregivers are asked three yes/no stem questions for each CU trait. In case of a yes response, the interviewer will ask for examples of everyday situations persistent over different settings, (e.g., Does ____ show his/her/their feelings and emotions openly to others? Please give some examples of this), the monthly frequency of the specific behavior, and for how long the symptom has lasted. After the interview, each CU trait is rated by the clinician as ‘not descriptive or mildly descriptive’ (0), ‘moderately descriptive’ (1), or ‘highly descriptive’ (2). If there are two CU traits rated as ‘highly descriptive’, LPE diagnosis is assigned. The CAPE 1.1 assessments in this study were intentionally conducted without using additional sources of information (e.g., files), even though guidelines recommend that interview data should normally be combined with such information (Frick, 2013). In accordance with the methodology by Hawes et al. (2020), the SPJ is administered following the interview with the primary caregiver. This approach is employed to ascertain the interrater reliability of the interview. The necessity for this approach is predicated on the requirement for standardized implementation across multiple study sites.

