**Research question 1:**

*Interrater reliability*

To ascertain interrater reliability, all CAPE interviews will be independently coded by a second rater in a double-blind (no information on questionnaire data and SPJ from the treating clinician) coding process. The secondary coder will either be a psychology student (master’s candidate), a trained child and adolescent psychotherapist, or a trained physician. We will use quadratically weighted Cohen’s κ to estimate interrater reliability.

*Convergent and divergent validity*

Pearson correlations are used to assess discriminative validity (empathy, emotion recognition, parental warmth, social competence) and convergent validity (proactive aggression, DBD, CU traits, aggressive behavior, parental strictness).

*Incremental validity*

Hierarchical regression analyses will be conducted to determine whether the dimensional CAPE score can serve as an incremental predictor of DBD, social competence, proactive aggressive behavior, empathy, emotion recognition, and the control variables of age and gender beyond the ICU.

*Group comparison of the specifier “with limited prosocial emotions”*

This study aims to investigate the hypothesis that children with or without CAPE LPE differ in levels of CU traits, DBD, and social competence, parental warmth/strictness, (reactive/proactive) aggressive behavior, empathy, and emotion recognition. To this end, an analysis of covariance (ANCOVA) will be performed. We will control for age, study site (waiting list, outpatient, daycare, or inpatient), traumatic event, anxiety (to account for primary and secondary CU traits), and sex in the ANCOVA models.

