**For research question 2:**

*Defining groups*

Patients with ‘highly descriptive’ in at least one CU Trait on the CAPE interview will be separated into two groups (primary or secondary CU traits), theory-informed by the experience of two interpersonal potentially traumatic events (≥2 = secondary CU traits) and by anxiety scores (T ≥ 70 = secondary CU traits). This approach requires that the SPJ assessment include at least one CU characteristic, thereby ensuring that the exploratory subgrouping is limited to patients who exhibit clinically relevant CU-related characteristics. It is imperative to acknowledge that this exploratory classification does not aspire to represent or supersede a formal LPE classification. We concur with Cecil et al. (2018) that data-driven methodologies, such as cluster analysis, are not feasible in a clinical context, where decisions are made according to cutoff points. Moreover, previous analyses have demonstrated that trauma allows for a distinction between primary and secondary CU traits (Cecil et al., 2018; Kimonis et al., 2012), and there is also evidence that anxiety effectively differentiates between the two forms (Todorov et al., 2025). Consequently, we adhere to the recommendations set forth by Craig et al. (2021) and undertake a comprehensive assessment of potentially traumatic experiences and anxiety levels. In this study, a cutoff of two potentially traumatic experiences will be used to account for severity and to model repeated interpersonal trauma (Karpman, 1941; Kimonis et al., 2012; Pueyo et al., 2022).

*Group comparison*

ANCOVA models assessing group differences between primary and secondary CU trait groups across relevant constructs (CU traits, emotion recognition, reactive aggressive behavior, depression, attention problems, anxiety, parental warmth/strictness, and DBD) will be conducted. We will control for age, study site (waiting list, outpatient, daycare, or inpatient), and sex in the ANCOVA models.

*Effect size and statistical assumption*

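### The ANCOVA covariate called study site lists treatment settings, so no described model adjusts for the two clinics

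*Protocol article*

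**What the plan says.** Section 2.2 of the protocol article gives the reason for using more than one clinic: "Participants are recruited from two independent clinical sites to improve the generalizability of results and to minimize potential site-specific biases". Section 2.5, on the CAPE, uses the same word for the clinics when it justifies the interview procedure: "The necessity for this approach is predicated on the requirement for standardized implementation across multiple study sites". Section 2.1 treats care setting as a separate matter: "Data will be collected in outpatient, inpatient, and day-clinic settings of Child and Adolescent Mental Health clinics".

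Section 2.6 then specifies the LPE group comparison: "We will control for age, study site (waiting list, outpatient, daycare, or inpatient), traumatic event, anxiety", and sex. For the comparison of primary with secondary CU traits it says: "We will control for age, study site (waiting list, outpatient, daycare, or inpatient), and sex in the ANCOVA models".

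The other analyses of research question 1 name no site term. For the correlations: "Pearson correlations are used to assess discriminative validity", with no covariates given. For the hierarchical regressions, section 2.6 mentions "the control variables of age and gender beyond the ICU". Section 2.4 sizes those regressions with "number of tested predictors: 2; total number of predictors: 7" and does not say what the seven are.

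**The concern.** The label and the listed levels of this covariate do not match. A child at either clinic may be on a waiting list, an outpatient, a day patient or an inpatient, so the four levels do not identify the clinic. An analyst who follows section 2.6 would adjust for setting and could believe that site had been handled.

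This matters because the grouping variable is a structured clinical judgement. Clinics may differ in how readily a trait is rated highly descriptive, and in the patients they see. If the clinic that assigns LPE more often also has worse outcome scores among children of the same LPE status, part of the LPE difference is a difference between clinics, and it would be read as construct validity. If the differences run in opposite directions, a true association is diluted. Recruiting at two clinics does not remove such a difference unless the analysis takes the clinic into account.

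**Working it through.** **1. The places side by side**

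| Place | Meaning of site or setting |
|---|---|
| 2.1 | Settings: outpatient, inpatient, day clinic |
| 2.2 | Sites: two clinics |
| 2.5, CAPE | Study sites: the clinics |
| 2.6, both ANCOVAs | Study site: waiting list, outpatient, daycare, inpatient |
| 2.6, correlations | No covariate named |
| 2.6, regressions | Age, gender and ICU named; no site term |

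The article does not enter the clinic as a factor, stratum or cluster in any described model. In the regressions, age, sex, the ICU and CAPE make four predictors if the ICU enters as one score. Three of the seven are then unidentified.

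**2. The plan's ANCOVA sample sizes**

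Inputs (section 2.4): two groups, α = 0.05, power 0.95, f = 0.50 and f = 0.40. The test is an F test with 1 numerator df, denominator df = N − 2 − c (c = covariate df) and noncentrality λ = N·f².

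- LPE contrast: c = 7 (age 1, sex 1, trauma count 1, anxiety 1, setting 3). N = 55 gives λ = 55 × 0.25 = 13.75, denominator df 46, power 0.9525.
- Primary versus secondary: c = 5 (age 1, sex 1, setting 3). N = 84 gives λ = 84 × 0.16 = 13.44, denominator df 77, power 0.9515.

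The smallest N reaching 0.95 is 55 and 84 respectively, as stated, for every covariate count tried between 1 and 9.

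**3. The same with a two-level clinic term**

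- LPE contrast: c = 8, denominator df 45, power 0.9523. Required N stays 55.
- Primary versus secondary: c = 6, denominator df 76, power 0.9515. Required N stays 84.

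**4. Size of an unadjusted clinic effect (assumed values)**

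The article gives no clinic shares, no LPE rate by clinic and no clinic effects, so this step is an illustration. Let g be the clinic shift in the outcome at fixed LPE status (in SD), w the share of patients at clinic A, pA and pB the LPE rates, and p the overall rate.

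Bias before any covariate adjustment: b = g · w(1 − w)(pA − pB) / [p(1 − p)].

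With w = 0.5, pA = 0.60, pB = 0.40 and p = 0.50, the multiplier is 0.25 × 0.20 / 0.25 = 0.20.

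- g = 0.2: b = 0.04 SD
- g = 0.5: b = 0.10 SD
- pA = pB: b = 0, whatever g is

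Approximate type I error at N = 84 uses se = √(1 + g²w(1 − w)) / √(84·p(1 − p)) and Φ(−1.96 + b/se) + Φ(−1.96 − b/se). For g = 0.2, se = 0.219 and the error is about 5.4%. For g = 0.5, se = 0.225 and it is about 7.3%.

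**5. Against the planned effect**

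With two equal groups d = 2f, so f = 0.50 means d = 1.0. A bias of 0.04 to 0.10 SD is 4% to 10% of that.

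The shift g must be taken at fixed LPE status. If 0.5 SD were the raw gap between clinics and d were 1.0, LPE itself would account for 1.0 × 0.20 = 0.20 SD of it. The remaining 0.30 SD would give b = 0.30 × 0.20 = 0.06 SD.

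**The case against.** The strongest case on the other side is that this is a labelling slip in a condensed article, with model coding left to a fuller plan. That would hold if the covariate were merely unspecified. But the article does specify it, twice, with levels that contradict its name, so the text has to be reconciled either way.

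Several other counterpoints stand, and they limit the size of the problem:

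- The LPE contrasts are already adjusted for setting, age, sex, trauma count and anxiety, which would take up some of any case-mix difference. Only the remainder is at issue.
- A difference in rating severity alone, with no outcome difference between clinics at fixed LPE status, does not create spurious validity.
- Section 2.5 describes training, at least three years' experience and continuous supervision, which should narrow rating differences. Blind second coding helps less. By section 1.4 it relies on written notes and ticked items, so a clinic's habits of probing and note-taking can reach both raters, and κ does not remove them from the contrasts.
- Zero-order correlations are a normal choice for convergent and divergent validity.

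A reader might infer more than the article supports. Section 1.4 cites LPE prevalences of 60% and 21.6%; entered in the formula with equal clinics and shifts of 0.2 to 0.5 SD, they give 0.08 to 0.20 SD. Those rates come from a detention centre and an outpatient sample in different studies, so they say nothing about these two clinics and serve at most as an outer bound. Nor is d = 0.41 in section 2.4 a fair yardstick, since it is cited for research question 2. A reader might also assume that each clinic uses its own interviewers, or that a clinic term is definitely absent from the regressions. The article does not state the first, and the seven unlisted predictors leave the second open.

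**Conclusion.** The mismatch is certain on the text: in both ANCOVA specifications, study site means treatment setting, and no described model names the clinic. What follows for the results is conditional. A bias in the LPE contrasts needs the clinics to differ both in LPE rate and in outcome at fixed LPE status, beyond what the listed covariates absorb. The documents contain nothing from which to compute it. Under the assumed 60% versus 40% LPE rates, equal clinic sizes and a shift of 0.2 to 0.5 SD, it is about 0.04 to 0.10 SD before covariate adjustment, small beside the planned effect. The article does not support a conclusion that the validity findings would be mainly clinic differences. The point should be corrected because the better model is plain and nearly free.

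**What to change.** In section 2.6, rename the four-level covariate treatment setting in both ANCOVA paragraphs. Add a two-level clinic indicator to all ANCOVA models and to step 1 of the hierarchical regressions, and list the regression predictors so that the count in section 2.4 can be checked. Partial correlations given clinic may be reported beside the planned Pearson correlations as an optional sensitivity analysis.

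The cost is one degree of freedom per model. The required ANCOVA sizes stay at 55 and 84. No new data collection should be needed, since each child is recruited through one of the two clinics.

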**For research question 2:**

*Defining groups*

Patients with ‘highly descriptive’ in at least one CU Trait on the CAPE interview will be separated into two groups (primary or secondary CU traits), theory-informed by the experience of two interpersonal potentially traumatic events (≥2 = secondary CU traits) and by anxiety scores (T ≥ 70 = secondary CU traits). This approach requires that the SPJ assessment include at least one CU characteristic, thereby ensuring that the exploratory subgrouping is limited to patients who exhibit clinically relevant CU-related characteristics. It is imperative to acknowledge that this exploratory classification does not aspire to represent or supersede a formal LPE classification. We concur with Cecil et al. (2018) that data-driven methodologies, such as cluster analysis, are not feasible in a clinical context, where decisions are made according to cutoff points. Moreover, previous analyses have demonstrated that trauma allows for a distinction between primary and secondary CU traits (Cecil et al., 2018; Kimonis et al., 2012), and there is also evidence that anxiety effectively differentiates between the two forms (Todorov et al., 2025). Consequently, we adhere to the recommendations set forth by Craig et al. (2021) and undertake a comprehensive assessment of potentially traumatic experiences and anxiety levels. In this study, a cutoff of two potentially traumatic experiences will be used to account for severity and to model repeated interpersonal trauma (Karpman, 1941; Kimonis et al., 2012; Pueyo et al., 2022).

*Group comparison*

ANCOVA models assessing group differences between primary and secondary CU trait groups across relevant constructs (CU traits, emotion recognition, reactive aggressive behavior, depression, attention problems, anxiety, parental warmth/strictness, and DBD) will be conducted. We will control for age, study site (waiting list, outpatient, daycare, or inpatient), and sex in the ANCOVA models.

*Effect size and statistical assumption*

In accordance with the study by Neo et al. (2023), the *κ* values will be interpreted using Altman’s (1991) guidelines: values ranging from 0.80 to 1.00 will be classified as indicating very good agreement, values ranging from 0.60 to 0.80 will be classified as indicating good agreement, values ranging from 0.40 to 0.60 will be classified as indicating moderate agreement, values ranging from 0.20 to 0.40 will be classified as indicating fair agreement, and values below 0.20 will be classified as indicating poor agreement. Effect sizes will be estimated using η^2^ (small = 0.01, medium = 0.06, and large = 0.14 (Cohen, 1988)). To correct for multiple testing, Alpha levels will be Bonferroni-Holm corrected.

Before conducting the ANCOVA, a comprehensive series of prerequisite checks will be conducted. These checks encompass the identification of potential outliers (±3 standard deviations), the assessment of linearity between covariate and dependent variables through scatter plots, the evaluation of homoscedasticity via residual plots, and the confirmation of the normal distribution of the disturbance variables through histograms of the standardized residuals and P-P plots. Independence of observations will be addressed through the study design. Multicollinearity is evaluated using variance inflation factors (VIFs). The assumption of homogeneity of regression slopes will be tested by examining the interaction between the grouping variable and the covariate.

## 3. Ethics and Trial Registration

The Ethics Committee of the Medical Faculty at Friedrich-Alexander Universität Erlangen-Nürnberg approved the project (committee reference number: 24-112-S) on 28 May 2024. In addition, the project was registered in the German clinical trials registry (ID: DRKS00035428).

Participants will be informed about the study procedure, its benefits, and associated risks. Before the study begins and interviews are recorded, written informed consent will be obtained from parents and the child’s legal guardians. Participation in the survey can be withdrawn at any time without giving reasons. All procedures follow the principles of the Declaration of Helsinki, 1964, and Good Clinical Practice.

